### Data collection

All patients will be assigned a unique participant code. The key will be stored separately from the data. We plan to collect the following baseline data (age, sex, performance status (WHO performance score), American Society of Anesthesiologists physical status, body mass index, weight loss, decreased appetite, diabetes mellitus, previous liver or pancreatic diseases, smoking and alcohol status and tumor markers (CEA and CA19–9)) using the data management system Castor EDC (Castor Electronic Data Capture, Ciwit BV, Amsterdam, The Netherlands). Data on diagnostic procedures (like endoscopic imaging and biopsies), treatment and clinical follow-up will be collected during the entire study period by the local treating physicians or the trial coordinators using Castor EDC. Patients will be asked to fill in validated quality of life questionnaires (EORTC QLQ-C30 and QLQ-PAN26) at baseline and after 3-, 6- and 12-months follow-up.

### MRI and CT

MRI scans will be made on a 3 T scanner with T2 weighted imaging, using an intravenous gadolinium-based contrast agent with a T1 weighted pre-contrast, arterial and portal-venous phase, DWI with b-values of 50, 500 and 800 s/mm^2^ and with a Magnetic Resonance Cholangio-Pancreatography (MRCP). CECT scans are performed with intravenous iodine contrast agent with a pancreatic phase of the upper abdomen, a portal venous phase of the entire abdomen. Additionally, the chest will be staged using chest CT. MRI and CECT will be performed at baseline and after 3-, 6- and 12-months follow-up, the schedule is displayed in a flowchart in Fig. 1.

**Fig. 1 Fig1:**
[figure not shown]
Flowchart of study schedule and procedures

### Interpretation of MRI and CT

All MRI and CECT scans will initially be evaluated by the local radiologist and the findings will be included in the clinical decision making. The MRI and CECT scans will also be independently evaluated by a second radiologist blinded for findings of the first evaluation and the clinical outcome. If the MRI and CECT of one patient is evaluated by the same radiologist a minimum interval of 6 weeks will be used to minimize the risk of recall bias.

The MRI and CECT scans will be analyzed for local resectability and suspicious liver lesions. Number of liver lesions, lesion size, liver segment, presumed diagnosis of suspicious liver lesions (indeterminate or malignant) and imaging characteristics on MRI will be noted.

### Reference standard

Indeterminate or malignant liver lesions will be further investigated histopathologically. The first step in obtaining histological proof of suspected liver lesions on CECT and/or MRI is transabdominal ultrasound of the liver. Biopsy will be performed of visible liver lesions and analyzed with routine histological examination. When lesions are not visible or there is no histological proof of the visible lesions, the next step is surgical exploration (laparoscopic or open) in (borderline) resectable pancreatic cancer. In case liver lesions are identified a frozen section is performed. Hereafter, patients are treated according to standard care protocol.

For patients with suspected liver lesions without histopathological proof, follow-up imaging with paired CECT and MRI at 3, 6 and 12 months will serve as an alternative reference standard. Lesions that are growing or increasing in number over time will be considered metastases.

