**Methods:**

The DIA-PANC study is a prospective, international, multicenter, diagnostic cohort study investigating diffusion-weighted, contrast-enhanced MRI for the detection of liver metastases in patients with all stages of pancreatic cancer. Indeterminate or malignant liver lesions on MRI will be further investigated histopathologically. For patients with suspected liver lesions without histopathological proof, follow up imaging with paired CT and MRI at 3-, 6- and 12-months will serve as an alternative reference standard.

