## Background

Pancreatic ductal adenocarcinoma (PDAC) is one of the most lethal forms of cancer and expected to become the second leading cause of cancer-related deaths before 2030. Developments in pancreatic cancer diagnostics, surgical techniques and treatment have hardly improved the survival rate in the past 40 years. The 5-year relative survival rate as reported by the American Cancer Society remains only 8% [1, 2].

Only 5–25% of all patients are eligible for surgery, to date the only potential cure [3]. Approximately 40–45% of all patients with pancreatic cancer have metastatic disease at diagnosis and 40% of all patients have locally advanced disease with tumor involvement of surrounding vessels or organs. At the time of surgery, approximately 10–20% of the patients are considered unresectable because of unexpected liver metastasis, peritoneal carcinomatosis or locally advanced disease [4–6].

More than 50% of all liver metastases develop in the first six months postoperatively [7]. These liver metastases are most likely already present at the time of diagnosis and have not been identified pre-operatively, as they are too small to be detected by routine preoperative ultrasound and contrast-enhanced CT (CECT) [8, 9].

CECT is highly accurate in assessing the relationship of the tumor to critical arterial and venous structures, since their involvement can preclude surgical resection. However, CECT has a poor sensitivity (38–76%) for the detection and characterization of liver metastases [7, 10–13], especially for subcentimeter metastases, which are often present in pancreatic cancer [14]. This leads to futile surgical treatment with all the associated morbidity, mortality and costs. Moreover, patients who were explored with curative intent and were found unresectable due to peritoneal or liver metastases had a worse overall survival compared to patients with unexpected locally advanced disease [15].

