### Primary outcome

The sensitivity and specificity of Gd-enhanced MRI with DWI for the detection of liver metastases in patients with pancreatic cancer.

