#### Analysis

Analysis will be done using SPSS (IBM Corp., Armonk, New York, USA). Continuous variables will be summarized with standard descriptive statistics including mean, standard deviation, median, and range. Categorical variables will be summarized with frequencies. A *p*-value less than 0.05 is considered statistically significant.

For the analysis of the diagnostic accuracy (sensitivity and specificity) a 2 × 2 cross tabulation will be made comparing MRI and CECT to histopathology and follow up. Performance of CECT and Gd-enhanced MRI with DWI will be compared using McNemar’s test. We will report the changes made in patient management in a descriptive manner. Median and 1-year survival will be reported. Survival endpoints (disease free survival and overall survival) will be analyzed using Kaplan-Meier plots. Survival curves are compared using the log rank test. We will compare the results of both readers to determine the inter-observer variability. A Cohen’s Kappa (k value) of 0.81–1.00 is interpreted as excellent, 0.61–0.80: substantial agreement, 0.41–0.60: moderate agreement, 0.21–0.40: fair agreement, and 0.00–0.20: poor agreement.

We partly anticipated missing data by introducing the composite reference standard of follow up. Unfortunately, missing data still can occur when, for instance, a patient suspected of having metastatic disease, does not have histopathological confirmation and dies before the composite reference standard follow up could take place. If necessary, additional analysis will be performed to determine the robustness of the results and to deal with missing data.

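### The reference standard is written only for patients with suspected liver lesions; patients negative on both baseline scans have no stated rule, which leaves the primary sensitivity open to upward bias

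*Protocol article*

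**What the plan says.** All references are to the protocol article.

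- Primary outcome: "The sensitivity and specificity of Gd-enhanced MRI with DWI for the detection of liver metastases in patients with pancreatic cancer".
- Reference standard, first part: "Indeterminate or malignant liver lesions will be further investigated histopathologically". The work-up described there starts from lesions suspected on CECT, MRI or both.
- Reference standard, second part: "For patients with suspected liver lesions without histopathological proof, follow-up imaging with paired CECT and MRI at 3, 6 and 12 months will serve" as the alternative. The Methods paragraph of the Abstract carries the same restriction: "For patients with suspected liver lesions without histopathological proof, follow up imaging with paired CT and MRI at 3-, 6- and 12-months will serve".
- Positivity on follow-up: "Lesions that are growing or increasing in number over time will be considered metastases".
- MRI and CT, with no restriction to any subgroup: "MRI and CECT will be performed at baseline and after 3-, 6- and 12-months follow-up".
- Analysis, again without restriction: "a 2 × 2 cross tabulation will be made comparing MRI and CECT to histopathology and follow up".
- Background, on liver metastases that appear in the first six months after surgery: "These liver metastases are most likely already present at the time of diagnosis and have not been identified pre-operatively".

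**The concern.** Sensitivity needs the diseased patients whom the scans missed, and specificity needs the disease-free patients. Many of both will have no suspected lesion at baseline, either because nothing was seen or because what was seen was called benign. The Reference standard section gives these patients neither a positive nor a negative definition. Its follow-up criterion concerns growth or an increase in number. It does not say how to treat a first lesion in a liver that was clear at baseline, and it sets no time limit.

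If the section is applied as written, two outcomes are possible:

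- **Scan-negative patients are counted as true negatives.** Metastases missed by both scans then leave the denominator of sensitivity, which becomes detection among metastases that at least one scan saw.
- **Scan-negative patients are left out of the table.** Sensitivity is biased in the same way. Specificity is also distorted, because it is then estimated only among patients with a lesion suspected on at least one scan.

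The Background expects occult disease at diagnosis, at least in operated patients, so such misses are foreseeable. The recruitment target of 138 patients with liver metastasis also depends on who counts as reference-positive. If the choice is left open, it could be made after the follow-up results are known.

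**Working it through.** **1. The plan's own figure.** The Sample size section gives an expected sensitivity of 90%, Z = 1.96, 138 patients with metastasis, 40% prevalence, 80% analysable and about 433 patients in total. It states no half-width. With n = Z² × Se × (1 − Se) / d² and d = 0.05:

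- n = 1.96² × 0.9 × 0.1 / 0.05² = 138.3
- 138.3 / 0.40 / 0.80 = 432.2, or 433 rounded up

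Both stated figures reproduce, so the arithmetic is not at fault. The 5-point half-width is inferred.

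**2. Formula for the bias.** Let c be CECT sensitivity, s overall MRI sensitivity, and m the share of truly metastatic patients missed by both scans. If those patients are not counted as diseased, apparent MRI sensitivity = s / (1 − m).

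**3. Inputs.** c = 38% to 76% (Background). MRI sensitivity is 84% in the investigators' retrospective study (Background). That study covered patients without liver metastases on CECT, so 84% is read as sensitivity among CECT-negative patients. Then m = (1 − c) × (1 − 0.84):

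- c = 38%: m = 0.62 × 0.16 = 0.0992
- c = 76%: m = 0.24 × 0.16 = 0.0384

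**4. Two assumptions about overlap.**

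*Independent misses.* Overall MRI sensitivity is then also 84%.

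- c = 38%: 0.84 / 0.9008 = 93.3%, a bias of +9.3 points
- c = 76%: 0.84 / 0.9616 = 87.4%, a bias of +3.4 points

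*CECT detections nested in MRI* (MRI sees everything CECT sees). True overall MRI sensitivity is c + (1 − c) × 0.84, and apparent sensitivity is 100%.

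- c = 38%: 0.38 + 0.62 × 0.84 = 90.1%, a bias of +9.9 points
- c = 76%: 0.76 + 0.24 × 0.84 = 96.2%, a bias of +3.8 points

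**5. CECT.** With the same m, apparent CECT sensitivity is 0.38 / 0.9008 = 42.2% (+4.2 points) or 0.76 / 0.9616 = 79.0% (+3.0 points).

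**6. The same effect in counts.** The expected analysed cohort is 433 × 0.80 ≈ 346, of whom about 346 − 138 = 208 have no recognised metastasis. Suppose MRI detects 124 of 138 (89.9%). Adding double-missed patients as false negatives gives:

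| Added | Sensitivity |
|---|---|
| 0 | 124/138 = 89.9% |
| 5 | 124/143 = 86.7% |
| 10 | 124/148 = 83.8% |
| 20 | 124/158 = 78.5% |

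The 10 and 20 are about 5% and 10% of the 208. These counts are illustrations; the documents give none.

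**The case against.** The strongest reply is that the article can be read more broadly. Follow-up scans are scheduled for everyone, the Analysis section tabulates both scans against histopathology and follow-up without limiting it to suspected lesions, and the Discussion expects follow-up to reveal metastases after resection. Histology from lesions found at surgery could also enter the table. MRI-negative metastases that CECT sees already count as MRI misses. The article is condensed, a full protocol exists, and the flowchart is not shown, so a rule for scan-negative patients may be stated elsewhere.

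Much of this stands. A reader might infer that metastases missed by both scans can never count as false negatives and that the reported sensitivity is therefore certain to be inflated. The documents do not support that: the data that could reveal the misses are planned, and only double-negative patients are affected.

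A reader might also compute a 16-point bias by taking 84% as overall MRI sensitivity and setting apparent sensitivity to 100%. That fails, because the 84% comes from patients without liver metastases on CECT. In the nested case true overall sensitivity is then 90% to 96%, and the gap is 4 to 10 points.

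What does not stand is that this is only omitted detail. The article has a dedicated section saying whom the reference standard covers, and it restricts both parts to suspected lesions. The Abstract repeats the restriction for the follow-up part. Even under the broad reading, nothing says whether a metastasis first seen at 3, 6 or 12 months is a baseline miss or new disease.

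**Conclusion.** The point holds in limited form. The stated reference standard does not cover patients negative on both baseline scans, and the unrestricted wording in the MRI and CT and Analysis sections does not supply the missing classification. If the rule is applied literally, the sensitivity of both scans is biased upward; if scan-negative patients are dropped, specificity is distorted too.

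The size cannot be derived from the documents. For MRI sensitivity it is about +3 to +9 points under independent misses and about +4 to +10 points under nesting. Both ranges rest on CECT sensitivity of 38–76%, on 84% MRI sensitivity among CECT-negative patients carrying over to an all-stage cohort, and on double-missed patients receiving no follow-up classification. Against an inferred half-width of about 5 points, a bias in these ranges could match or exceed the sampling uncertainty. That is reason enough to settle the rule before the primary analysis.

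**What to change.** Extend the Reference standard section to every analysed patient, using the scans already planned. For a patient without a suspected lesion at baseline:

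- **Reference-positive (a false negative)** if a liver metastasis is shown by histology or at surgery, or first appears on follow-up imaging within a prespecified window.
- **Reference-negative** if free of liver metastasis through that window.

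Prespecify one primary window and repeat the analysis with the other scheduled times. Six months is one candidate, with the 3- and 12-month scans as sensitivity analyses. The Background supports six months only for metastases appearing after surgery, so its use in unresected patients should be stated as an assumption. Align the Abstract and Analysis wording with the rule.

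The cost is wording and analysis, with no extra scans. The downside is that some truly new metastases will count as misses, so sensitivity will look somewhat less favourable. The 3-month analysis limits this but does not remove it, and patients who die before the first follow-up scan remain unclassified by imaging.

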### Safety and ethics

There is a low risk and low burden for patients participating in this study. Patients might benefit from study participation due to possible improvement of detection of liver metastases. The contrast agent used for MRI has few known side effects and rarely leads to a severe allergic reaction [29]. Extra CECT scans might be performed in some study patients with the associated radiation and contrast exposure. Patients diagnosed with pancreatic cancer have a 5-year overall survival of 8%. Radiation-induced cancer has a latency period that substantially exceeds 5 years. Therefore, the health risk for this specific oncologic patient group is almost negligible.

MRI can lead to earlier detection of liver metastases, however in some patients these lesions might be too small to biopsy. Consequently, we cannot always provide the patient certainty about the nature of the liver lesions detected with MRI. Furthermore, in follow-up local recurrence or metastases might be detected before a patient has symptoms. This may be seen as a disadvantage by some individuals.

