The DIA-PANC trial hypothesizes a superior value of MRI for the detection of liver metastases compared to CECT. To reliably determine the diagnostic accuracy the gold standard is histopathology of the liver lesions. Considering it is not always possible, and sometimes even unethical, to obtain histopathological proof of every lesion, follow-up is used as a reference standard. Hence, we are able to simultaneously gather information on (early) local recurrence or metastases after resection, disease progression, and therapy response evaluation on MRI and CECT.

In conclusion, the DIA-PANC trial is expected to report high-level evidence of the diagnostic accuracy of MRI for the detection of liver metastases compared to CECT, resulting in significant value for clinical decision making, guideline development and improved stratification for treatment strategies and future trials. Furthermore, DIA-PANC will contribute to our knowledge of liver metastases regarding incidence, imaging characteristics, their number and extent, and their change in time with or without treatment. When our hypothesis is confirmed, it will enhance the worldwide implementation of MRI and consequently improve personalized treatment of patients suspected of PDAC.

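### For lesions without histology, growth seen on follow-up MRI alone can define a metastasis, so baseline MRI is partly graded by MRI; the plan should bound this with an analysis by type of confirmation

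*Protocol article*

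**What the plan says.** The primary outcome (Methods, Primary outcome) is "The sensitivity and specificity of Gd-enhanced MRI with DWI for the detection of liver metastases in patients with pancreatic cancer". CECT accuracy is a secondary outcome.

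Under Reference standard, histology comes first: "Indeterminate or malignant liver lesions will be further investigated histopathologically". Lesions visible on transabdominal ultrasound are biopsied. For lesions that are not visible or remain unproven, "the next step is surgical exploration (laparoscopic or open) in (borderline) resectable pancreatic cancer". Where no histology is obtained, "follow-up imaging with paired CECT and MRI at 3, 6 and 12 months will serve as an alternative reference standard", with the rule "Lesions that are growing or increasing in number over time will be considered metastases". The rule names no modality and does not ask for agreement between CECT and MRI.

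Safety and ethics accepts that histology will sometimes be out of reach: "MRI can lead to earlier detection of liver metastases, however in some patients these lesions might be too small to biopsy".

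Under Analysis, histopathology and follow-up together supply the truth column of the 2 x 2 tables for both tests. "Performance of CECT and Gd-enhanced MRI with DWI will be compared using" McNemar's test. The Discussion gives the direction expected: "The DIA-PANC trial hypothesizes a superior value of MRI for the detection of liver metastases compared to CECT".

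**The concern.** Baseline MRI is the test under evaluation, and follow-up MRI helps decide whether baseline MRI was right. As written, growth or multiplication seen on MRI alone is enough to label a patient as having metastases.

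The exposed patients are those with a lesion seen on MRI but not on CECT that is too small to biopsy, or who do not undergo surgical exploration. Such lesions matter to the comparison, because MRI's expected advantage lies in small lesions that CECT misses.

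If such a lesion is benign but is confirmed on later MRI, the patient leaves MRI's false-positive cell, enters its true-positive cell, and becomes a false negative for CECT. In McNemar's test on sensitivity the error adds only to the MRI-positive, CECT-negative cell. At stake are the specificity half of the primary outcome and the MRI-CECT sensitivity comparison.

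**Working it through.** **The plan's own figure.** n = 1.96² x 0.90 x 0.10 / 0.05² = 138.3, which matches the stated 138 (the half-width of 0.05 is inferred; the text gives none). Total: 138.3 / 0.40 / 0.80 = 432.2, in line with the stated 433 or so. These figures are not in dispute.

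**Inputs for the illustration.**
- 138 reference-positive patients (Sample size). Analysable total 433 x 0.80 = 346, leaving 208 reference-negative.
- Apparent MRI sensitivity 90% (Sample size): 124 of 138.
- Apparent CECT sensitivity 76%, the top of the 38-76% range in Background: 0.76 x 138 = 104.88.
- Apparent MRI specificity 95% (assumption; the article cites 88% for 3 T MRI and 96-100% in the earlier prospective study): 10.4 false positives among 208.
- k patients whose positive label rests on follow-up MRI alone, of whom a share q are wrong. **Neither k nor q is in the document.** Wrong labels: w = k x q, all CECT-negative.

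**Formulas for the true values.**
- MRI sensitivity = (124 - w) / (138 - w)
- CECT sensitivity = 104.88 / (138 - w)
- Difference = (19.12 - w) / (138 - w)
- MRI specificity = 1 - (10.4 + w) / (208 + w)

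| k | q | w | MRI sens. | CECT sens. | Difference (points) | MRI spec. |
|---|---|---|---|---|---|---|
| 0 | - | 0 | 89.9% | 76.0% | 13.9 | 95.0% |
| 14 | 10% | 1.4 | 89.8% | 76.8% | 13.0 | 94.4% |
| 14 | 25% | 3.5 | 89.6% | 78.0% | 11.6 | 93.4% |
| 28 | 25% | 7 | 89.3% | 80.1% | 9.3 | 91.9% |

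The first row is what the trial would report. The others are the truth behind that report under each assumption.

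**How large k can be.** At 76% CECT sensitivity, only 0.24 x 138 = 33.1 reference-positive patients are CECT-negative. If the two tests read independently, about 0.90 x 33.1 = 29.8 of these are MRI-positive. If every MRI miss is also a CECT miss, about 19 are. So k = 28 would require roughly 94% of MRI-only positives (28/29.8) to have no support from biopsy, surgery or later CECT. It is near the ceiling.

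**Lower CECT sensitivity, same w = 7.** At 57% (78.66 detected) the difference falls from 45.34/138 = 32.9 to 38.34/131 = 29.3 points. At 38% (52.44 detected) it falls from 71.56/138 = 51.9 to 64.56/131 = 49.3 points. For a given number of errors the effect on superiority shrinks, although more MRI-only patients could then exist.

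**Cross-check from the other side.** Take true values: MRI sensitivity 90%, CECT 76%, 207 patients without metastases (138/0.40 - 138), and a share of MRI-only false positives upgraded by follow-up MRI. With true specificity 88% (24.8 false positives), upgrading 10%, 25% or 50% turns a true 14.0-point difference into 15.5, 17.7 or 21.1. With 96% it becomes 14.5, 15.3 or 16.5. The direction is the same throughout; the size depends on the assumptions.

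**What an MRI-free reference does.** Treat all k = 14 as unverified. Sensitivities become 110/124 = 88.7% for MRI and 104.88/124 = 84.6% for CECT, a difference of 4.1 points, whether the 14 are excluded or counted as reference-negative. MRI specificity stays at 95.0% if they are excluded and becomes 1 - 24.4/222 = 89.0% if they are counted as negative. The true difference in that scenario is 13.0-11.6 points, so the MRI-free result lies well below the truth.

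**The case against.** Histology comes first and is not confined to lesions that CECT shows. A reader might infer that an MRI-only lesion can be confirmed only by MRI. The text does not support that: biopsy, surgical exploration in (borderline) resectable disease, or growth on the paired follow-up CECT can all confirm it. Nor does the article say that small lesions will mostly fall to imaging follow-up; it says only that some may be too small to biopsy.

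The overlap is also partial. Baseline positivity rests on DWI signal, whereas the reference asks for growth or increase in number, so a false positive must appear to change before it is upgraded. CECT is in the reference too, and a CECT-only lesion could be confirmed by CECT. The Discussion justifies follow-up because histology is not always possible or ethical.

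These points stand and limit the size. They do not remove the problem. The rule still accepts growth on MRI alone, and the article's own account of CECT leads one to expect more MRI-only than CECT-only lesions. The reason given for follow-up does not address the overlap with the index test. The robustness analyses under Analysis are conditional and belong to the paragraph on missing data.

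An unseen analysis plan might contain the extra analyses. The point therefore rests on the positivity rule that the article does state and on its use as truth for both tests.

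**Conclusion.** The concern holds as partial incorporation of the index test in its reference standard, limited to patients without histology. When the wrongly confirmed lesions are MRI-only, the error favours MRI. Its size cannot be derived from the document.

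Under the assumptions shown, a moderate case (14 patients, 10-25% wrong) costs about 1 to 2 points of the sensitivity difference and 0.6 to 1.6 points of MRI specificity. The case near the ceiling costs 4.6 points and 3.1 points. MRI sensitivity hardly moves, from 89.9% to 89.3% at most, so the primary outcome is touched mainly through specificity.

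Two stronger readings fail. One is that the bias could explain away MRI's advantage. In these scenarios a positive difference remains, and larger counts soon become impossible: 41 MRI-only patients (30% of 138) would exceed the 33 who are CECT-negative at 76%. The other is that superiority should be claimed only if it survives an MRI-free reference. That would make the comparator the sole imaging reference and reverse the bias.

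What remains is a worthwhile, cheap improvement to the plan.

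**What to change.** Keep the main reference standard and add the following:

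1. For each patient counted positive on follow-up, record whether growth or increase in number was seen on CECT, on MRI or on both.
2. In the Analysis section, commit to repeating the MRI and CECT accuracy estimates and McNemar's test with positives confirmed on MRI alone treated as unverified: first excluded, then counted as reference-negative.
3. Report accuracy separately for histology-verified and imaging-verified patients.
4. Present the main and MRI-free analyses as a bracket. Do not make the superiority claim conditional on the MRI-free analysis.

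The cost is one recorded item per follow-up positive, some wording and extra tables. The paired scans are already scheduled, and the sample size does not change. The drawback is that the MRI-free analysis is conservative for MRI, because CECT misses small metastases; the report should say so beside the result.

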**Discussion:**

The DIA-PANC trial is expected to report high-level evidence of the diagnostic accuracy of MRI for the detection of liver metastases, resulting in significant value for clinical decision making, guideline development and improved stratification for treatment strategies and future trials. Furthermore, DIA-PANC will contribute to our knowledge of liver metastases regarding incidence, imaging characteristics, their number and extent, and their change in time with or without treatment. It will enhance the worldwide implementation of MRI and consequently improve personalized treatment of patients with suspected pancreatic ductal adenocarcinoma.

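### The follow-up rule recognises metastases only by growth or increase in number, so one that shrinks or stays stable under treatment through 12 months cannot become reference-positive

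*Protocol article*

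**What the plan says.** The primary outcome is "The sensitivity and specificity of Gd-enhanced MRI with DWI for the detection of liver metastases in patients with pancreatic cancer" (Protocol article, Primary outcome). Truth comes from histology where it can be had. Where it cannot, the Reference standard section turns to imaging: "For patients with suspected liver lesions without histopathological proof, follow-up imaging with paired CECT and MRI at 3, 6 and 12 months" serves as the alternative. The only follow-up criterion stated there is "Lesions that are growing or increasing in number over time will be considered metastases". Lesions that shrink, vanish or stay the same are not mentioned, and neither is treatment given between scans.

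Histology will be missing for an unknown share of patients. All stages are eligible, but after an unsuccessful ultrasound or biopsy "the next step is surgical exploration (laparoscopic or open) in (borderline) resectable pancreatic cancer", so other patients have no surgical route to proof. Safety and ethics adds that "in some patients these lesions might be too small to biopsy".

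Nothing suggests that treatment is withheld during follow-up. The paragraph on obtaining histology ends "Hereafter, patients are treated according to standard care protocol", and Data collection records treatment throughout the study. The Discussion plans to use the follow-up scans for "disease progression, and therapy response evaluation on MRI and CECT", and the abstract's Discussion expects to learn about metastases and "their change in time with or without treatment".

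The Analysis section compares MRI and CECT with histopathology and follow-up in a 2 × 2 table.

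**The concern.** The protocol expects treated metastases to change in either direction, but its follow-up rule recognises only progression. Whether a true metastasis counts as one then depends on how well treatment worked, which has nothing to do with whether baseline MRI was right.

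A responding or stable metastasis has two possible fates in a binary table. If it is reference-negative, a correct MRI call becomes a false positive, and specificity and sensitivity both fall. If it is set aside, patients leave the analysis according to treatment response. In both cases the number of patients with established metastases is understated, and that number drives the recruitment stop.

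A second, smaller gap concerns the increase-in-number limb, which is not tied to the suspected baseline lesion. A new metastasis appearing within the 12 months could confirm an unchanged benign lesion and credit MRI with a detection that it did not make.

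**Working it through.** **The plan's own figures.** Precision formula: n = z²p(1 − p)/d² with z = 1.96 and p = 0.90 (Sample size). The half-width d = 0.05 is inferred, because the text gives 0.05 only as α. n = 3.8416 × 0.09/0.0025 = 138.3. With 40% prevalence and 80% analysable, 138.3/0.40/0.80 = 432.2, rounded up to 433. The protocol's 138 and 433 reproduce and are not in dispute.

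**Base table.** 433 × 0.80 ≈ 346 analysable, of whom 138 have metastases and 208 do not. Sensitivity is 90% (protocol). True specificity of 95% is an assumption; the background cites 96–100% from one prospective study and 88% for 3 T MRI from a meta-analysis.

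- True positives: 0.90 × 138 = 124.2
- False negatives: 13.8
- True negatives: 0.95 × 208 = 197.6
- False positives: 10.4

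**Reclassification.** Let f be the share of MRI-positive metastasis patients without histology, and s the share of those whose lesions neither grow nor increase in number at any visit. The documents give neither. Only the 124.2 MRI-positive patients can move from true to false positive, so k = 124.2 × f × s. The 13.8 false negatives are assumed to stay reference-positive.

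- Specificity = 197.6/(208 + k)
- Sensitivity = (124.2 − k)/(138 − k)

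| f and s | k | Specificity | Sensitivity | Reference-positive |
|---|---|---|---|---|
| 20%, 20% | 5.0 | 197.6/213.0 = 92.8% | 119.2/133.0 = 89.6% | 133.0 |
| 40%, 40% | 19.9 | 197.6/227.9 = 86.7% | 104.3/118.1 = 88.3% | 118.1 |
| 60%, 60% | 44.7 | 197.6/252.7 = 78.2% | 79.5/93.3 = 85.2% | 93.3 |

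For scale, the 95% half-width for specificity is 1.96 × √(0.95 × 0.05/208) = 3.0 points. The middle row is off by 95 − 86.7 = 8.3 points.

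**If the same patients are excluded instead.** They do not enter the false-positive cell, so they do not lower specificity. Sensitivity still falls by the same formula, to 88.3% in the middle row, because only MRI-positive metastases have been removed. Patients whose MRI call was wrong and whose lesion does not grow would be excluded by the same logic. If 40% of the 10.4 false positives went this way, specificity would read 197.6/(208 − 4.2) = 97.0%, too high rather than too low.

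**Effect on the recruitment stop.** At the maximum of 465, the expected number of analysable metastasis patients is 465 × 0.80 × 0.40 = 148.8. The middle row loses 19.9/138 = 14.4% of them, leaving 148.8 × 0.856 ≈ 127, short of 138. The first row loses 3.6% and leaves about 143, so the target is still met.

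**The case against.** The strongest objection is textual. The rule gives a sufficient condition; it does not say that a lesion which fails to grow is benign. A reader might infer that every responding metastasis is bound to become a false positive, but the document does not say so. The Sample size section allows for 20% of patients who cannot be analysed optimally, and the Analysis section offers additional robustness analyses if necessary. Exclusion is therefore at least as open a reading, and under it the specificity loss does not arise. This part of the objection stands. It does not remove the problem: growth or increase in number remains the only follow-up route to a positive result, and exclusion that depends on response is also a bias. The missing-data text gives death before follow-up as its example, whereas a lesion that was scanned and shrank is observed, not missing.

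It can also be said that an article may leave such detail to the full protocol. That would hold if the article were silent. Here it states the rule, and the rule conflicts with the treatment response that it expects on the same scans.

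Three further inferences are not supported:

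- That the increase-in-number limb has no time limit: the schedule ends at 12 months.
- That MRI will confirm its own findings, so that truth should rest on histology plus follow-up CECT: the text specifies paired CECT and MRI, and the background gives CECT a sensitivity of 38–76%, so that remedy would build CECT's misses into the truth.
- That all 138 metastasis patients are exposed to the move: only the roughly 124 MRI-positive ones are.

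Finally, the size is uncertain. A lesion that responds at 3 months and grows by 12 is still counted, so s covers only lesions that never progress in the window. Continued recruitment up to 465 also offsets part of the lost count.

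**Conclusion.** The point holds in this form: for suspected lesions without histology, a true metastasis that shrinks or stays stable under treatment at all visits cannot become reference-positive. The consequence is a false positive or a response-dependent exclusion, plus a lost case towards 138. Which of the two applies cannot be told from the document.

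Under the false-positive reading, with both shares between 20% and 60%, specificity reads 92.8% to 78.2% against 95%, and sensitivity 89.6% to 85.2% against 90%. Under exclusion, sensitivity is affected in the same way and specificity is not lowered. These figures rest on assumed shares and an assumed 95% specificity; they show what the rule can do and do not forecast the result. The untied increase-in-number limb works in the opposite direction, in MRI's favour, and cannot be relied on to cancel the main effect.

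Because the rule defines truth for the primary outcome, it should be settled before the reference standard is assigned.

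**What to change.** Amend the follow-up part of the Reference standard section so that each suspected lesion without histology is classified as follows:

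- **Metastasis** if that lesion grows, or if it shrinks or disappears during systemic anti-cancer treatment.
- **Benign** if it is unchanged to 12 months without such treatment.
- **Unresolved** if it is unchanged under such treatment. Report sensitivity and specificity three times: with these lesions counted as positive, as negative and excluded.

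Tie the increase-in-number limb to the suspected baseline lesion, so that a new lesion during the 12 months does not by itself confirm an unchanged one. State which of these classes counts towards 138.

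Treating response as evidence of metastasis is a convention and should be labelled as one. The change concerns classification for analysis only and leaves patient care as it is. The cost is a wording amendment and two additional tabulations; treatment, serial scans, lesion size and liver segment are already recorded. The downside is that a small unresolved group makes the primary result a set of bounds instead of a single figure.
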